**Fig. 2 Fig2:**
[figure not shown]
(**a**) Fixture design, (**b**) Establishment for femur experimental biomechanical study and (**c**) Loading system configuration

The test fixture was designed to provide a compressive force to the femoral head through the acetabular cup and a tensile force simulating the contraction of the abductors to the greater trochanter. The phase of gait to be simulated was chosen to be the single-leg stance phase at the moment immediately after heal strike when the highest hip joint load acts [40, 41]. According to previous reports, the abductors exert by far the most relevant load at this phase of gait and thus the other muscles can be neglected in a first approximation [39, 42]. In our experimental fixture, a metallic rod is attached to the lateral aspect of the greater trochanter, using epoxy glue, to simulate the hip abductor muscles. A load cell is used to monitor the force exerted by the abductors in the metallic rod under the different loading conditions. The manufactured jig is presented in Fig. 2b attached to an electromechanical testing machine and applied on an artificial bone. In the same figure the indicator of the load cell measuring the force on the greater trochanter is shown.

#### Loading configuration

A great variability exists in the literature regarding both the magnitude and the direction of forces being included among the different experimental set-ups. In our study, the loading configuration was chosen in accordance with the set-up used by Cristofolini et al. for applying the hip force and the abducting force to the femur [39, 43] (Fig. 2c). According to this loading configuration, a hip joint force (2.47 body weights (BWs) at 29^0^ to the femoral diaphysis) and an abducting force (1.55 BWs, at 40^0^ to the femoral diaphysis) will be applied to the femur.

The non-implanted and implanted femurs will be placed on the testing machine using the custom-made jig. Loads will be applied on the head of the intact composite femur and on the heads of the 28-mm prostheses through the acetabular cup. The specimens will be initially loaded with 100 N and the load will be increased by increments of 100 N up to a total of 1000 N. The strain patterns will be recorded for each loading level.

#### Digital image correlation (DIC)

The DIC equipment includes two digital cameras that could view the cortex of the femurs from different view angles (Fig. 3). On the femur to be tested a random speckle pattern is created. The non-implanted and implanted femurs will each be placed into the testing machine and load up to 1000 N will be applied according to the configuration described above. The undeformed and deformed speckle patterns on the bone are captured at each loading level. Using the Aramis software the captured imaged are analyzed and detailed 3D contour maps of strain fields are produced for each data set.

**Fig. 3 Fig3:**
[figure not shown]
The digital image correlation equipment

#### Statistical analysis

Statistical analysis will be performed using SPSS Statistics (Version 23, IBM SPSS, Armonk, NY, USA). Normal distribution of the parameters of interest, namely axial construct stiffness, failure load, and cycles to failure in each study group will be screened with Shapiro-Wilk test. Homogeneity of variances between the groups will be checked with the Levene test. Significant differences between the two groups will be checked with paired-samples *t* test. A *P* = .05 level of significance will be set for all statistical tests.

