**Fig. 1 Fig1:**
[figure not shown]
The two different stems that will be compared in the study **a**. Trilock Bone Preservation Stem, **b**. Minima S

In the experimental study, the transmission of forces as measured by cortical surface-strain distribution in the proximal femur will be evaluated using DIC, first on the non-implanted femur and then on the implanted TRI-LOCK Bone Preservation Stem (BPS) and Minima S femoral stems. The strain patterns of the non-implanted femur will served as the control group. The primary outcome would be to check the presence of adequate metaphyseal anchorage and the effect of the two different-design short stems on the strain patterns compared to the unimplanted femur.

Finite element parametric models of the bone, the stem and their interface will be also developed. Finite element predictions of surface strains in intact and implanted composite femurs, after being validated against biomechanical testing measurements, will be used to assist the comparison of the stems by deriving important data on the developed stress and strain fields, which cannot be measured through biomechanical testing.

A prospective randomized comparative clinical study between these two types of short stems, will be also conducted to determine (1) their clinical performance up to 2 years’ follow-up using validated scoring instruments and gait analysis parameters; (2) stem fixation and bone remodeling using a detailed radiographic analysis and (3) incidence and types of complications if any.

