#### Study aims

Although both stems belong to the same short-stem family, the Tri-Lock BPS is a stem with a geometrical design similar to conventional long stems (its design is based on its clinically successful predecessor, the Tri-Lock standard stem), but shorter with a narrower distal segment. On the other hand, the Minima S stem is even shorter, has an anatomic shape following the natural curvature of the medial calcar, preventing breach of the greater trochanter and a medially sidecut tip to reduce the risk of contact with the cortical medial wall.

We can hypothesize that the above variations, regarding stem length and geometric design, may create differences in strain distribution and thus dissimilar biomechanical behaviors. Specifically, we sought to determine if the implantation of a shorter, anatomically shaped stem would produce a pattern of strain distribution closest to normal, reduce the risk of distal locking and proximal offloading. Therefore, strain patterns after implantation of the Minima S stem are compared to both strain patterns without an implanted stem and strain patterns following implantation of the Trilock BPS stem.

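### The bench study's statistical section analyses load at failure and cycles to failure, which the described 1000 N strain experiment cannot produce, and does not name strain

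*Protocol article*

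**What the plan says.** All places are in the Protocol article.

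- **Primary outcome of the bench experiment** (Background, text after Fig. 1). It has two parts: adequate metaphyseal anchorage, and "the effect of the two different-design short stems on the strain patterns compared to the unimplanted femur".
- **Contrasts** (Biomechanical study, Study aims). "strain patterns after implantation of the Minima S stem are compared to both strain patterns without an implanted stem", and also to the patterns after Tri-Lock BPS implantation.
- **Specimens** (Preparation of the femurs). There are seven composite femurs, with three different ones for each stem, and a set of three tests for every specimen.
- **Loading** (Loading configuration). Starting at 100 N, "the load will be increased by increments of 100 N up to a total of 1000 N". The section on digital image correlation repeats the ceiling: "load up to 1000 N will be applied according to the configuration described above".
- **Measurement** (Loading configuration). "The strain patterns will be recorded for each loading level".
- **Analysis** (Statistical analysis of the biomechanical study). The section screens "Normal distribution of the parameters of interest, namely axial construct stiffness, failure load, and cycles to failure in each study group", checks homogeneity of variance with Levene's test, and continues: "Significant differences between the two groups will be checked with paired-samples" t test. A .05 "level of significance will be set for all statistical tests".

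**The concern.** The analysis section appears to belong to a different experiment, one with destructive and cyclic testing. It is not merely brief. It gives a closed list of parameters, and that list does not match what will be measured. An analyst who followed it literally would have nothing to enter for two of the three parameters, and would find no instruction for the strain data that the experiment is built to collect.

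The bench study is a headline aim of the project. It has its own primary outcome, its measurements are to validate the finite element models, and the resulting stress findings are to be related to the clinical results. What is analysed, and how, should therefore agree with what is measured.

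**Working it through.** The protocol gives no sample-size, power or error-rate figure for the bench study, so there is no stated number to reproduce. The check compares each analysed parameter with the described procedure.

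**1. Can each named parameter be observed?**

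- *Load at failure.* This needs loading until the construct breaks. The schedule stops at 1000 N, and each specimen is tested three times, which is incompatible with breaking it. No procedure is described.
- *Cycles to failure.* This needs cyclic loading. The schedule is a single stepwise ramp of 1000/100 = 10 levels, repeated as three tests. No procedure is described.
- *Axial stiffness.* This could in principle be derived from load and displacement. The article does not say that displacement is analysed, but the set-up does not rule it out.

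Result: 2 of 3 named parameters have no procedure that could produce them.

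**2. Is the stated outcome among the analysed parameters?**

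Background and Study aims both make strain patterns the object of comparison, and the loading and imaging sections record strain at every level. The parameter list contains stiffness and two failure measures. Result: 0 of 3 named parameters is strain, and the word does not occur in the section.

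**3. Could 1000 N be meant as a failure test?**

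The loading configuration sets the hip joint force at 2.47 body weights. The article does not say whether 1000 N is that force or the machine load on the beam. Assuming it is the hip force:

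- implied body weight = 1000 / 2.47 = 405 N, and 405 / 9.81 = about 41 kg;
- for assumed body weights of 60 to 80 kg, one stance load would be 2.47 × 60 × 9.81 = about 1454 N to 2.47 × 80 × 9.81 = about 1938 N.

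Under that assumption the ceiling lies below one ordinary stance load. This only supports step 1, which does not depend on it.

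**4. Does the named test fit strain if strain is put in its place?**

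- *Stem against stem.* There are three different femurs per stem and no pairing is defined, so the specimens are independent as described. Levene's test, planned in the same section, also belongs with independent groups. A paired t test does not fit.
- *Stem against intact.* Intact femurs = 7 − (2 × 3) = 1. A single specimen has no between-specimen variance, and its three repeat runs measure repeatability, not variation between femurs. A two-group test between stems does not address this contrast at all.

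**The case against.** The strongest reply is that this is a bench experiment on composite bone. The randomized study has its own endpoints, sample size and analysis, and none of them draws on this section. That is correct, and it limits the point to the bench component.

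A second reply is that the parameter list is attached grammatically to the normality screen, while the sentences that follow are general and could be stretched to cover strain. A reader might otherwise infer that strain will receive no test whatever. The text does not support going that far: what it shows is that strain is not named. The generous reading is nevertheless strained, because the list is introduced as the parameters of interest. It also does not reach the comparison with the intact femur.

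A third reply is that a journal article condenses, and that regions, load level and summary measure belong in the full plan. This stands as far as those details go. A reader might infer that regions will be picked after the contour maps have been seen, or might multiply the ten load levels by some number of regions to count comparisons. Neither inference is supported. The article says nothing about when regions are chosen and gives no number of regions, and successive load steps on one specimen are strongly dependent. Condensation does not explain a list that names the wrong parameters, however. A fuller plan that analysed strain would contradict this section, and one that followed it would leave strain out.

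**Conclusion.** The point holds as a contradiction within the article. Two of the three parameters in the bench study's statistical section cannot come from the experiment as described. Strain, which is one part of the two-part primary outcome and the subject of both planned contrasts, is absent from that section.

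The conclusion rests on the described procedure: no loading to failure, no cyclic loading, and three tests per specimen. An accidental break below 1000 N would yield a load at failure by chance, but not by plan. The count of one intact femur follows from seven femurs with three per stem, and assumes that none of the six is also tested before implantation. The article speaks of the intact femur in the singular and describes embedding the implanted femurs after implantation.

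A reader might infer that all three parameters are unobservable, or that the clinical trial's inference is affected. Neither follows: stiffness may be derivable, and the clinical analysis is separate.

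**What to change.** Reconcile the biomechanical Statistical analysis section with Background, Study aims, Preparation of the femurs, Loading configuration and Digital image correlation:

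1. Delete load at failure and cycles to failure, or describe the tests that would produce them.
2. Name the strain parameter: one summary per femur, averaged over its three repeat runs, either at a stated load level or as the slope of strain on load over the ten steps. Fix the regions in advance among the surfaces that are actually imaged. The article says only that two cameras view the cortex from different angles, so those surfaces should be stated first.
3. Compare Minima S with Tri-Lock BPS using a test for independent specimens, three against three, unless a pairing is defined and justified.
4. Report each stem against the intact femur descriptively, or against a fixed reference value, and say that one intact femur allows no between-specimen inference.
5. State how metaphyseal anchorage, the other part of the primary outcome, will be judged.

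The cost is mainly redrafting before the strain data are analysed, since strain recording is already planned. It would be more than redrafting if the failure parameters are kept, because they need added destructive and cyclic tests, or if formal inference against the intact condition is wanted, because that needs more intact specimens.

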#### Preparation of the femurs

Seven fourth generation, medium composite, femurs from Sawbones Europe (Malmö, Sweden) with identical design and material properties will be used in accordance to previous biomechanical studies [13, 32–37]. Three different composite femoral bones for each prosthesis will be prepared by the same investigator ([name]) according to the manufacture’s surgical technique. Also, a set of three tests will be repeated for each specimen. The quality of implantation in terms of correct implant size and positioning (anteversion) will be assessed using antero-posterior and lateral radiographs. After the radiographic evaluation, the implanted femurs will be fixed into a steel cylinder using a standardized embedding procedure based on a previously reported femur-aligned reference system [38]. During the embedding procedure, a custom alignment fixture will be used, ensuring that the central axis of the femur through fossa piriformis coincides with the central axis of the cylinder. The femurs will be fixed in neutral position on the sagittal plane, using the posterior condylar surface as reference for rotational alignment and at 11^0^ of adduction in frontal plane, to simulate the physiological inclination during single-leg stance [39]. The distal condyles of the intact femur will be embedded into the steel cylinder using the same embedding protocol as described above. The proximal end of each femur will then be prepared for DIC measurements. A layer of matt-white paint, followed by black speckles will be applied creating a high contrast, random speckle pattern.

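### Bench study: the normality and variance screens on three femurs per stem say almost nothing, carry no stated consequence and do not fit the paired t test that follows

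*Protocol article*

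**What the plan says.** The sample is set out in the Protocol article, Biomechanical study, Preparation of the femurs. The stock is "Seven fourth generation, medium composite, femurs from Sawbones Europe". Of these, "Three different composite femoral bones for each prosthesis will be prepared by the same investigator", and "a set of three tests will be repeated for each specimen". That gives three independent specimens per stem, nine readings per stem, and one femur left over as the intact reference.

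The analysis is in the Statistical analysis section of the same study. It names "axial construct stiffness, failure load, and cycles to failure" as the parameters. Each is to be tested for normality group by group: "in each study group will be screened with Shapiro-Wilk test". For spread, "Homogeneity of variances between the groups will be checked with the Levene test". The stems are then compared with a paired-samples t test, stated without condition. The ."05 level of significance will be set for all statistical tests", which includes the screens.

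The section does not say what happens if a screen fails, names no alternative test, describes no pairing of femurs, and does not say whether the unit of analysis is the femur or the single reading.

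**The concern.** A screen for an assumption is useful only if it can detect a breach and if the plan says what follows. With three values per group neither test has much to work on, so a pass will be reported as support that the data did not give. A fail will quite often be chance, and the analyst then has to decide what to do after seeing the data.

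The screens also do not match the test they precede. A paired t test assumes that the within-pair differences are roughly normal. It makes no assumption of equal variances, and normality within each stem's group is not the quantity that matters. Preparation of the femurs gives each stem its own bones, so pairing them would be arbitrary. At stake are the precision and the error rate of the bench comparison of the two stems; the clinical trial is not affected.

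**Working it through.** **Plan's own figure.** The document gives no power or error rate for the bench study, so there is none to reproduce. Only the count can be checked: 7 = 3 + 3 + 1 intact.

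**Inputs.** n = 3 femurs per stem and three repeats per femur (Preparation of the femurs); level .05 for every test (Statistical analysis). Assumed, because not stated: two-sided tests; the version of Levene, so both are shown.

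**1. Shapiro-Wilk at n = 3.** For three ordered values, W = [(x3 − x1)²/2] / Σ(xi − x̄)², and the exact P is (6/π)[arcsin√W − arcsin√0.75]. Rejection at .05 over 400,000 simulated samples:

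| Distribution | Rejected |
|---|---|
| Normal | 5.0% |
| Uniform | 6.0% |
| t, 3 df | 5.3% |
| Exponential | 7.3% |
| Lognormal (sigma 1) | 8.2% |
| Chi-square, 1 df | 12.7% |

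More than 90% of exponential and lognormal samples pass.

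**2. Levene at 3 against 3 (normal data).**

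| SD ratio | Mean-based | Median-based |
|---|---|---|
| 1 | 4.8% | 0% |
| 2 | 9.0% | 0% |
| 3 | 15.8% | 0% |
| 5 | 27.7% | 0% |
| 10 | 43.6% | 0% |

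**3. False alarms with ideal data.** Each parameter has two Shapiro-Wilk tests and one Levene test. If independent, 1 − 0.95³ = 14.3%. Simulated with mean-based Levene: 13.6%. Median-based Levene never rejected, which leaves the two Shapiro-Wilk tests: 1 − 0.95² = 9.75%, simulated 9.7%.

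**4. Paired test on unpaired femurs.** With three arbitrary pairs the paired t test has 2 degrees of freedom (critical value 4.30). A pooled unpaired test would have 4 (critical value 2.78); Welch lies between. Simulated power for normal data with equal variance:

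| True difference (between-femur SDs) | Paired | Welch |
|---|---|---|
| 2 | 29% | 37% |
| 3 | 51% | 68% |
| 4 | 71% | 89% |

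With no true difference, Welch rejects 3.4% when variances are equal, and 4.3%, 5.2% and 5.8% at SD ratios of 2, 3 and 5. It therefore stays near the 5% level without a variance check.

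**5. If the nine readings were taken as nine pairs.** The plan does not say this, but does not exclude it. The result depends on w, the within-femur SD as a fraction of the between-femur SD, which the document does not give. False-positive rate with no true difference: 36% at w = 0.1, about 33% at w = 0.3, 28% at w = 0.5, 18% at w = 1. Welch on femur means stays between 3% and 4% throughout.

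**The case against.** The best defence is that the screens do no harm. The t test is stated without condition, so as written a failed screen changes nothing, and the 14% counts flags, not altered conclusions. What follows a failure may also be set out in a fuller document. This stands, and it limits the point: deleting the screens alone would change no result.

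A reader might go further and infer that a failed screen sends the analysis to a rank test, where the smallest exact two-sided P at 3 against 3 is 2/C(6,3) = 0.10, so that the study could then never show a difference. The document does not support this. The bench section names no rank test; the only one, Wilcoxon, belongs to the clinical primary endpoint. Even under that assumption the limit is not absolute, since an uncorrected normal approximation gives 0.0495. Nor should the 14% be compounded over the three parameters, which would be measured on the same femurs and need not be independent.

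It is also fair that mean-based Levene is not blind to extreme imbalance (28% at an SD ratio of 5, 44% at 10). At ratios of 2 to 3 it still misses at least 84% of cases.

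Finally, one might run the screens on nine readings per stem, where Shapiro-Wilk would reject 39% of exponential and 55% of lognormal samples. That gain comes only from counting repeats on one bone as independent specimens.

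The defence does not reach the mismatch between the screens, the paired test and the separate femurs. That is in the text as it stands.

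**Conclusion.** The point holds in limited form. With three femurs per stem the two screens are close to uninformative, raise a false alarm for about one parameter in seven under ideal data (mean-based Levene; one in ten with median-based), have no stated consequence, and test something other than the assumption of the paired t test. That test does not suit separate femurs with no described pairing. It costs about 17 percentage points of power at a difference of 3 between-femur SDs (51% against 68%), assuming normal data, equal variances and a two-sided .05 level. If the repeats were entered as nine independent pairs, false positives would be about 33% at an assumed within-femur SD of 0.3 times the between-femur SD, and 18% to 36% over the range examined.

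The documents do not show that the bench conclusion hangs on chance screen results, or that the study loses all ability to find a difference. This is a minor, easily mended weakness in the bench analysis.

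**What to change.** In the Statistical analysis section of the Biomechanical study, remove the Shapiro-Wilk and Levene screens and the paired test. State one analysis in advance: average the three repeat tests to one value per femur; compare the stems with an unpaired Welch t test, reporting the difference with its 95% confidence interval; and show all individual femur values. Where a measure can yield only one reading per femur, as with load at failure, use that reading.

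The cost is a short rewording, with no new specimens or tests. Welch gives up some power against a pooled t test (68% against 78% at 3 SDs in the same simulation). That is the price of not relying on an equal-variance assumption that three femurs per stem cannot check.

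### The laboratory comparison of the two stems names a paired-samples t test, but each stem sits in its own three femurs and nothing pairs them

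*Protocol article*

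**What the plan says.** The design is in the protocol article under Biomechanical study, Preparation of the femurs:

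- The material is "Seven fourth generation, medium composite, femurs from Sawbones Europe", described as bones "with identical design and material properties will be used in accordance to previous biomechanical studies".
- "Three different composite femoral bones for each prosthesis will be prepared by the same investigator", so three femurs carry the Tri-Lock BPS and three others carry the Minima S.
- "The distal condyles of the intact femur will be embedded into the steel cylinder" by the same procedure as the implanted ones. The section thus treats the intact femur as a specimen in its own right.
- On replication: "Also, a set of three tests will be repeated for each specimen".

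The analysis is in the Statistical analysis section of the same study. It names axial construct stiffness, failure load and cycles to failure, and screens normality within each group with the Shapiro-Wilk test. It then says "Homogeneity of variances between the groups will be checked with the Levene test", followed by "Significant differences between the two groups will be checked with paired-samples" t tests at the .05 level. It does not say how pairs are formed or how the three repeats are handled.

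**The concern.** A paired t test analyses within-pair differences, so each observation in one group needs a definite partner in the other. Such a partner could be the same specimen tested under both conditions, or a left and right bone from one donor. The femur preparation section describes neither. The test named for the stem comparison therefore does not fit the design. It also sits badly with its own paragraph, because a between-group check of equal variances is an assumption check for independent samples.

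Anyone following the text would have to invent the pairs. With three femurs per stem, that choice could decide whether a stem difference is declared. The bench comparison matters to the wider study, since the Finite element analysis section intends to relate the stress results to the clinical findings.

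**Working it through.** **Inputs from the article.** Three femurs per stem, three repeat tests per femur (3 × 3 = 9 readings per stem), seven femurs in all (3 + 3 + 1 = 7), significance level .05. Sidedness is not stated; two-sided is assumed. The article gives no power figure for the bench study, so there is none to reproduce.

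**Assumptions, because the article gives no values.** The true difference d between stems, in SDs of the femur-level values, and the within-femur correlation (ICC) of repeat tests. Both are shown as ranges.

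**Step 1: is there a pairing?** Three different femurs per stem rules out the same bone carrying both stems. Nominally identical synthetic bones have no donor or side to match on. No test sequence links one Tri-Lock femur to one Minima S femur. The groups are independent.

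**Step 2: cost of three arbitrary pairs.**

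- Degrees of freedom: paired 3 − 1 = 2; independent 3 + 3 − 2 = 4.
- Two-sided 5% critical t: 4.303 on 2 df; 2.776 on 4 df.
- Arbitrary pairing leaves the standard error of the difference at SD × √(2/3) and induces no correlation. Both tests therefore have noncentrality d × √(3/2). At d = 3 this is 3 × 1.225 = 3.67.
- Power from the noncentral t distribution:

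| d (SDs) | Paired, 3 pairs | Independent, pooled |
|---|---|---|
| 2 | 0.29 | 0.46 |
| 3 | 0.51 | 0.78 |
| 4 | 0.71 | 0.95 |

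- Difference needed for 80% power: 4.62 SDs paired, 3.07 SDs pooled independent.
- Simulated type I error is 0.050 for both tests.
- The Welch version has less power than the pooled test at this size. At d = 3 simulation (200,000 runs) gives 68%. The gain over arbitrary pairing is thus 78 − 51 = 27 points for the pooled test and 68 − 51 = 17 points for Welch.

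**Step 3: a separate question, the repeat tests.** Simulation with no true difference, three femurs per stem and three repeats each, entering all nine readings per stem as if independent (200,000 runs per setting; unpaired values were not tabulated for the two lowest ICCs):

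| ICC | Paired, 9 pairs | Unpaired, 9 vs 9 | Unpaired on femur means, 3 vs 3 |
|---|---|---|---|
| 0 | 0.050 | 0.050 | 0.050 |
| 0.05 | 0.061 | – | – |
| 0.1 | 0.072 | – | – |
| 0.2 | 0.096 | 0.101 | 0.050 |
| 0.5 | 0.180 | 0.187 | 0.050 |
| 0.8 | 0.281 | 0.283 | 0.050 |
| 0.9 | 0.320 | 0.313 | 0.050 |

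The two nine-reading columns are nearly the same. Inflation comes from counting repeats as independent, not from pairing. Averaging within femur removes it at every ICC tried.

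**The case against.** **The damage may be small.** On three arbitrary pairs the paired test keeps its 5% error rate, so it creates no false positives. If the stems differ greatly, little power is lost: at 6 SDs the paired test has 93% against 99% for Welch. This stands. The case against the test is that it does not fit the design, depends on an arbitrary matching and wastes power at moderate differences.

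**A reader might infer that the plan leads to strong false-positive inflation.** The documents do not support that. Nowhere does the article say that the nine readings will serve as nine pairs, and averaging of repeats is a detail an article may leave to the full protocol. Two of the three named parameters, failure load and cycles to failure, can be obtained only once per femur. The ICC is also unknown. The Limitations section stresses low variability between composite specimens, so low values belong in the range, although implantation differences or very repeatable tests could make it high. Inflation is a conditional risk, and an unpaired test on the same readings would share it.

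**Pairing might be meant in another way.** The Abstract and Background describe testing first without and then with an implant. That could at most pair intact with implanted bone, never one stem with the other, and the count of 3 + 3 + 1 argues against it. Pairing by load step or surface location is conceivable, but those readings come from the same few femurs and are not independent replicates.

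**It may be a slip of the pen.** Possibly; the Levene check suggests that an independent test was intended. The text still names the wrong test.

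**Conclusion.** The point holds for the stem-versus-stem comparison in the laboratory study: a paired-samples t test is specified for two independent groups of three femurs. Read as three arbitrary pairs, type I error is unaffected. Degrees of freedom are halved, and at an assumed difference of 3 specimen SDs power is 51%, against 78% (pooled) or 68% (Welch). That loss depends on the assumed d.

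The handling of repeats is a second, conditional matter. If they are entered as independent readings, type I error lies anywhere from about 6% (ICC 0.05) through 10% (0.2) and 18% (0.5) to 32% (0.9), paired or unpaired.

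The clinical endpoints, sample size and analysis of the randomized comparison are not touched. How implanted femurs are compared with the intact femur is a different question, and this point does not settle it.

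**What to change.** In the Statistical analysis section of the biomechanical study, replace the paired-samples t test with an independent-samples t test on one value per femur, the mean of its three repeat tests, 3 versus 3. A mixed model on the individual readings with femur as a random effect is an alternative. Either way, name the femur as the unit of analysis and report the difference between stems with its 95% CI. Both parts are needed, since dropping the pairing alone would not guard against counting repeats as independent.

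State whether the pooled or the Welch version is used. The Levene check fits the independent test and can stay. If Welch is chosen, any power statement should use its own lower figure (68% at 3 SDs, not 78%).

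The cost is a few words of text, with no extra bones or tests. Testing each of the six femurs intact before implantation would be an optional addition for the intact-versus-implanted question and is not part of this correction.
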